#### Safety outcomes and adverse events report

2.6.3

Safety will be assessed by monitoring adverse events (AEs), serious adverse events (SAEs), withdrawals, or treatment modifications caused by AEs. Additionally, this study includes safety indicators such as 12-lead electrocardiogram, blood routine examination, liver and kidney function tests, coagulation function, platelet aggregation rate, blood glucose and lipid profiles, as well as urine and fecal routine examinations, which will be performed at baseline and 4th, 12th, 24th weeks following randomized grouping.

#### CCTA acquisition and image analysis

2.6.4

CCTA examinations were performed using a GE Revolution CT scanner. Scanning parameters included a tube voltage of 120 kV and tube current of 370–450 mA, with automatic exposure control technology applied to adapt to patient body habitus. The scanning mode was selected as either prospective or retrospective ECG-gating based on heart rate, requiring only a single axial scan to complete image acquisition. Images were reconstructed with a slice thickness of 0.625 mm and a rotation time of 0.28 s. A non-ionic contrast agent (Ioversol injection, 350 mg/mL, Jiangsu Hengrui Pharmaceuticals Co., Ltd.) was administered intravenously at a rate of 5 mL/s, with a total volume of 1 mL/kg. Following contrast injection, 30 mL of normal saline was injected at the same rate using the Smart bolus tracking technique, with the descending aorta selected as the region of interest to achieve optimal arterial phase imaging at 80 HU. Images were reconstructed using the ASiR iterative reconstruction algorithm, with SSF2 selected as the optimal reconstruction kernel for subsequent analysis. Image analysis was performed using the dedicated CoronaryDoc V2.0 software [Yukun (Beijing) Network Technology Co., Ltd.]. The specific methods for analyzing the images are as follows:
(a)CT-FFR Assessment: CT-FFR was utilized as the core indicator of vascular function. The CT-FFR value was measured 2 cm distal to the stenotic lesion. For patients with multiple stenoses or multi-vessel involvement, the vessel with the most severe luminal stenosis and its most severe lesion were selected as the measurement point. The change before and after treatment was calculated (△CT-FFR = post-treatment − pre-treatment).(b)FAI Assessment: FAI was obtained to reflect the local inflammatory burden of the coronary artery. The FAI level was measured over a 10 mm length centered on the stenotic lesion. A higher value indicates more significant inflammatory infiltration of local adipose tissue. For patients with multiple stenoses, the most severe lesion was selected, and its change was dynamically tracked (△FAI = post-treatment − pre-treatment).(c)WSS Assessment: WSS reflects the frictional force exerted by blood flow on the vascular endothelium. WSS values were extracted at the most severe stenotic lesion. The change before and after intervention was tracked (△WSS = post-treatment − pre-treatment).(d)High-Risk Plaque Characterization: Based on the CAD-RADS™ 2.0 criteria (2), morphological instability features of the plaques were identified. A plaque must exhibit two or more of the following features to be classified as a high-risk plaque: ① Spotty calcification: Small, punctate calcified deposits observed within the plaque; ② Low-attenuation plaque: Non-calcified plaque areas with internal CT attenuation values below 30 HU; ③ Positive remodeling: The ratio of the outer vessel diameter at the plaque site to the average of the normal proximal and distal reference diameters is >1.1; ④ Napkin-ring sign: The simultaneous presence of two features on the cross-sectional image of a non-calcified plaque: a central low-attenuation core surrounded by a ring-like peripheral rim with higher CT attenuation.

### Sample size

2.7

There are no studies using coronary artery hemodynamic parameters and FAI to evaluate the efficacy of traditional Chinese medicine in treating SCAD. This study is an exploratory trial and does not require sample size calculations (44). Sixty subjects will be recruited, with 30 participants allocated to each group, to investigate our research objectives.

### Data collection and management

2.8

This study utilizes paper-based CRFs for data collection. Physical examinations, scale scores, and results of tests and inspections shall be recorded on the CRFs promptly, accurately, completely, and in a standardized manner. Clinical monitors from the Clinical Pharmacology Research Institute of Xiyuan Hospital will review the data for completeness annually, after which the data will be transferred to two researchers for independent, double data entry to ensure accuracy. All data will be securely stored in a password-protected database, accessible only to the principal investigator for analysis and reporting. Other researchers will not have access to these data. The paper CRF forms and signed consent forms will be stored in a locked filing cabinet at Xiyuan Hospital. After all participants complete follow-up, all data will be stored electronically in the database of Xiyuan Hospital. participants' paper documents will be stored in a locked filing cabinet at Xiyuan Hospital for five years.

### Statistical analysis

2.9

According to the ITT analysis principle, the Full Analysis Set (FAS) is defined as the set of qualified cases that completed the study and analyzable drop-out cases, excluding excluded cases. The Per Protocol Set (PPS) is defined as the set of cases that comply with the trial protocol, have not concurrently used other drugs or treatments that may affect the trial results, have completed the full intervention and follow-up, and have completed the CRF as required. The Safe Set (SS) is defined as the set of cases that have received at least one dose of medication, possess baseline safety data, and have undergone at least one safety visit. Efficacy and safety will be evaluated based on the FAS, with the PPS used for sensitivity analysis.

Continuous variables will be described as mean ± standard deviation, categorical variables as frequency and percentage. Comparison of outcome measures between groups: continuous variables with a normal distribution will be analyzed using paired *t*-tests; those without a normal distribution will be analyzed using the Wilcoxon rank-sum test. Categorical variables will be compared using the *χ*^2^ test or Fisher's exact test. Subgroup analyses will be conducted based on whether patients have high-risk plaques (positive remodeling, low-attenuation plaque, spotty calcification, and napkin-ring sign) (2). Additionally, difficult-to-control and intergroup imbalanced confounding factors will be analyzed as covariates using analysis of covariance to eliminate their impact on efficacy evaluation. *P*-value <0.05 will be considered statistically significant. All statistical analyses will be performed using SPSS (version 25).

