#### Removal, dropout, and termination criteria

2.5.3

Participants will be excluded from the study if any of the following conditions are found after the study finishes: a. Participants don't meet the inclusion criteria or meet the exclusion criteria; b. Participants don't adhere to the medication regimen as specified in the study protocol; c. Participants have no post-treatment visit records; d. Participants used concomitant medications during the trial that may affect the evaluation of the efficacy and safety of SYF. Excluded cases should not be included in the efficacy analysis. However, the safety analysis should include those who have received at least one treatment and have at least one safety record.

If participants experience adverse events such as cardiac death, non-fatal myocardial infarction, acute heart failure, severe angina pectoris, severe arrhythmia, or coronary revascularization (PCI or CABG) during the study, or significant deviations occur during the intervention that hinder the evaluation of drug efficacy, participants will be withdrawn from the trial based on the clinical physician's judgment. Participants may voluntarily withdraw from the trial if they are dissatisfied with the efficacy, experience adverse reactions, plan to receive other treatments, or for other reasons leading to unwillingness to continue treatment. Participants who fail to complete the observation period specified in the trial will be considered dropout cases, regardless of the timing or reason. The reasons for dropout will be documented in the case report form (CRF) and included in the final data analysis.

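### The Full Analysis Set claims the ITT principle but drops non-adherers and users of interfering medication after the study ends, so the primary analysis is close to per-protocol

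*Protocol article*

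**What the plan says.** Section 2.9 (Statistical analysis) opens with "According to the ITT analysis principle" and then says that "the Full Analysis Set (FAS) is defined as the set of qualified cases that completed the study and analyzable drop-out cases, excluding excluded cases". The FAS is the main set for efficacy, and the PPS is the sensitivity analysis.

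The meaning of an excluded case comes from section 2.5.3 (Removal, dropout, and termination criteria): "Participants will be excluded from the study if any of the following conditions are found after the study finishes". Four conditions follow:

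- a: eligibility failure;
- b: failure to "adhere to the medication regimen as specified in the study protocol";
- c: participants who "have no post-treatment visit records";
- d: participants who "used concomitant medications during the trial that may affect the evaluation of the efficacy and safety of SYF".

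The consequence is explicit: "Excluded cases should not be included in the efficacy analysis". Such participants stay in the safety analysis if they were treated and have a safety record.

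The PPS in section 2.9 requires compliance with the protocol, no other drugs or treatments that could affect the results, the full intervention and follow-up, and a completed case report form.

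**The concern.** An ITT-type set keeps participants in their randomised arm whatever they do afterwards. Criteria b and d select on what participants did after randomisation. Someone who stays in the trial but takes the study drug irregularly because of intolerance, or adds another drug because symptoms persist, is removed from the primary comparison. If treatment affects who does this, the retained groups are no longer comparable and the estimate is biased, in a direction that cannot be known in advance.

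Non-adherence is foreseeable. Section 2.5.1 gives medication fatigue over 24 weeks as one reason for the lower dose in the second half. Section 2.5 permits several classes of background drug, while criterion d turns on whether a drug might affect evaluation, which is a judgement made at the end of the study.

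The sensitivity analysis is also weakened. If FAS and PPS leave out the same people, agreement between them says little about robustness.

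**Working it through.** The protocol gives no exclusion rate, power or effect size, so there is no stated figure to reproduce. The check is a comparison of the two sets, followed by an illustration.

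**1. FAS against PPS**

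| Participant | FAS (2.9 with 2.5.3) | PPS (2.9) |
|---|---|---|
| Non-adherent (b) | out | out |
| Interfering medication (d) | out | out |
| No post-treatment visit (c) | out | out |
| Eligibility failure (a) | out | out, as not protocol-compliant |
| Drop-out judged analysable | in | out |
| Adherent completer with completed CRF | in | in |

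The material difference is the analysable drop-out. Section 2.5.3 defines a drop-out as someone who did not complete the observation period. Section 2.6.1 measures CT-FFR, WSS and FAI only at baseline and week 24. An early drop-out therefore normally has no change score on a primary outcome, and the two sets nearly coincide there. For TCMSS and SAQ, also recorded at weeks 4 and 12 (section 2.6.2), they can differ.

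**2. Size of the bias (illustration)**

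From the documents: 30 per arm (section 2.7) and a 0.05 significance level (section 2.9). Assumed: a two-sided test, an independent-samples *t*-test, no true effect, and the exclusion shares and outcome deficits below.

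Let *e* be the share of the SYF arm removed, with none removed from placebo, and let *k* be how much worse the removed did than the retained, in SD. The retained mean exceeds the full-arm mean by *e* × *k*:

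- 0.10 × 0.5 = 0.05 SD
- 0.10 × 1.0 = 0.10 SD
- 0.20 × 0.5 = 0.10 SD
- 0.20 × 1.0 = 0.20 SD

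The standard error of the difference is √(1/n₁ + 1/n₂):

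- 30 vs 30: √(2/30) = 0.258 SD
- 27 vs 30: 0.265 SD
- 24 vs 30: 0.274 SD

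The chance of a significant result in favour of SYF (noncentral *t*, nominal 2.5%) is:

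| Analysed | Bias | Bias / SE | Chance |
|---|---|---|---|
| 27 vs 30 | 0.05 SD | 0.19 | 3.8% |
| 27 vs 30 | 0.10 SD | 0.38 | 5.6% |
| 24 vs 30 | 0.20 SD | 0.73 | 10.7% |

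**3. When both arms lose participants**

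Here *k* is measured from the full-arm mean, so the retained mean shifts by *e* × *k*/(1 − *e*). The table gives the total two-sided type I error by normal approximation (nominal 5%), for *k* from 0.5 to 1.0.

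| Removed, SYF / placebo | Bias (SD) | Type I error |
|---|---|---|
| 10% / 10% | 0 | 5.0% |
| 20% / 10% | 0.07–0.14 | 5.7–7.9% |
| 20% / 0% | 0.13–0.25 | 7.4–15.0% |
| 30% / 10% | 0.16–0.32 | 8.5–19.4% |

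If placebo loses more of its poor responders, the bias has the same size and works against SYF.

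**4. Precision**

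The difference detectable with 80% power is (1.96 + 0.84) × √(2/n). It is 0.72 SD at 30 per arm, 0.76 at 27, 0.81 at 24 and 0.87 at 21. The loss of precision is secondary to the bias.

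**The case against.** The strongest reply has four parts.

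- **Drop-outs are kept.** Section 2.5.3 treats those who leave through dissatisfaction, adverse reactions or plans for other treatment as drop-outs, and section 2.9 retains analysable ones. The FAS is therefore not word for word the PPS. This stands for the repeated outcomes. For the primary outcomes it helps only if a drop-out has a week-24 scan or the value is imputed, and it never restores participants caught by b or d.
- **Blinding.** Sections 2.3 and 2.4 keep allocation concealed through the primary analysis. That limits deliberate selection, but not exclusions that treatment itself brings about.
- **Magnitude.** Removal from one arm only is the extreme case in a matched-placebo trial. The deficits are assumed, and the link from non-adherence to an imaging outcome would have to run through symptoms or the effect of the drug. This stands: 10.7% is the top of a conditional range, and most of that range is smaller.
- **Exploratory status.** Section 2.7 calls the trial exploratory, and the half dose is meant to reduce medication fatigue. But section 2.1 declares a superiority trial and section 2.9 tests at 0.05. An attempt to limit non-adherence does not justify excluding those who remain non-adherent.

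An analysis plan not shown here could define which drop-outs are analysable or set an adherence threshold. It could not return b and d cases to the efficacy analysis without contradicting section 2.5.3.

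**Conclusion.** The concern holds. Sections 2.5.3 and 2.9 together fix an efficacy set that contradicts the ITT principle it claims, and for the three primary imaging outcomes that set is nearly the PPS. This is a rule the protocol states, not a detail it leaves out.

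The size cannot be known in advance. It depends on exclusions being related to outcome and differing between arms, which nothing in the protocol prevents. With 30 per arm, six exclusions are a fifth of an arm. Because this set carries the primary comparison, it should be corrected before the code is broken.

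**What to change.** In section 2.9, define the FAS as all randomised participants who took at least one dose, analysed in the arm to which they were randomised, whatever their adherence or concomitant medication.

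In section 2.5.3:

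- confine criteria b and d to the PPS;
- limit criterion a to eligibility failures that existed before randomisation, decided in a documented blind review before the A/B code is opened;
- drop criterion c as a ground for leaving the FAS, since the new definition covers those participants. Handling of missing week-24 scans can be set in the analysis plan.

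The PPS then differs from the FAS in substance and becomes a real sensitivity analysis.

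The cost is wording in two sections. No new data and no change to treatment are needed, though the estimate may be somewhat less favourable. Completed enrolment is no obstacle, but the change should be dated and made before unblinding.

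### Section 2.9 assigns safety to the FAS and leaves the Safe Set unused, contradicting section 2.5.3, which keeps excluded cases in the safety analysis

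*Protocol article*

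**What the plan says.** Section 2.9 (Statistical analysis) of the protocol article defines three populations:

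- The FAS is "the set of qualified cases that completed the study and analyzable drop-out cases, excluding excluded cases".
- The PPS is limited to participants who followed the protocol, used no interfering treatment and finished both the intervention and the follow-up.
- The Safe Set is the set of "cases that have received at least one dose of medication, possess baseline safety data, and have undergone at least one safety visit".

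The next sentence assigns the analyses: "Efficacy and safety will be evaluated based on the FAS, with the PPS used for sensitivity analysis". The Safe Set is not mentioned again.

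Section 2.5.3 (Removal, dropout, and termination criteria) says who becomes an excluded case, a status decided once the study is over. The reasons are (a) failing the eligibility criteria, (b) "Participants don't adhere to the medication regimen as specified in the study protocol", (c) having no visit record after treatment, and (d) "Participants used concomitant medications during the trial that may affect the evaluation of the efficacy and safety of SYF". The section then sets the scope of the exclusion: "Excluded cases should not be included in the efficacy analysis". For safety it says that "the safety analysis should include those who have received at least one treatment and have at least one safety record".

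The same section treats anyone who does not complete observation as a drop-out, whatever the cause.

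**The concern.** A safety set is defined so that every treated participant with safety information is counted, however well they followed the protocol. Here it is defined and then bypassed. The population named in its place is an efficacy set from which some participants have been removed for what happened after randomization.

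Three of the four exclusion reasons, (b), (c) and (d), can result from harm. A participant who cuts down or skips study drug because of a reaction may be judged non-adherent. One who becomes ill and never returns has no visit record. One who needs a new drug for an adverse event may be judged to have used interfering medication. None of these reasons makes an exception for an adverse event. Yet section 2.6.3 counts withdrawals and changes of treatment brought about by adverse events among the safety outcomes. A single occurrence could therefore be a safety outcome under 2.6.3 and a reason for removal from the safety population under 2.5.3 and 2.9 taken together.

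At stake are the adverse event rates and their comparison between arms, in a trial that sets out to evaluate safety as well as efficacy and has only 30 participants per group.

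**Working it through.** The plan states no figure that could be reproduced. The check compares the rules and then adds an illustration.

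**Step 1. Which set is safety evaluated on?**

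| Source | Safety population | Excluded cases in it? |
|---|---|---|
| 2.9, assignment sentence | FAS, with PPS as sensitivity set | No |
| 2.9, Safe Set definition | Dosed, with baseline safety data and a safety visit | Yes, if they meet these conditions, but no analysis uses the set |
| 2.5.3 | Treated, with a safety record | Yes |

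The first and third rows give opposite answers for excluded cases. The second row matches neither: it asks for baseline safety data, which 2.5.3 does not, and for a visit where 2.5.3 asks for a record.

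**Step 2. Who is lost if 2.9 is followed?**

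- Excluded cases (reasons a to d): out of the FAS, so out of the main safety results.
- Drop-outs who are analyzable and not excluded cases: stay in the FAS, including those who stopped because of an adverse reaction.
- Drop-outs who are not analyzable: out. The article does not define the term.
- Everyone who did not complete the intervention and follow-up: out of the PPS, so the sensitivity analysis of safety cannot recover anyone lost from the FAS.

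**Step 3. Illustration.** The arm size of 30 comes from section 2.7. The event and exclusion counts are assumptions, because the document gives none. With x participants having an event among n = 30, of whom k become excluded cases, the rate goes from x/30 to (x − k)/(30 − k). For x = 3, with exact (Clopper–Pearson) 95% intervals:

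| k | Rate | 95% interval |
|---|---|---|
| 0 | 3/30 = 10.0% | 2.1% to 26.5% |
| 1 | 2/29 = 6.9% | 0.8% to 22.8% |
| 2 | 1/28 = 3.6% | 0.1% to 18.3% |
| 3 | 0/27 = 0% | 0% to 12.8% |

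For the comparison between arms, assume 6 of 30 against 0 of 30. Fisher's exact test gives p = 0.024. If 3 of the 6 become excluded cases, 3/27 against 0/30 gives p = 0.10. If all 6 do, 0/24 against 0/30 gives p = 1.0. These figures assume exclusions in one arm only, although the rule applies to both.

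The direction also depends on who is excluded. If 3 participants without an event were excluded instead, the rate would rise from 3/30 = 10.0% to 3/27 = 11.1%. Rates are understated only if exclusion falls more on participants with events.

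**The case against.** The strongest reply is that this is a drafting slip in one sentence. Section 2.5.3 states the inclusive rule for safety in plain terms, and a Safe Set would hardly have been defined unless it was meant to be used. On that view the intention is clear and nobody would be lost. The intention is indeed plausible. But 2.9 is the section an analyst works from, and it names the FAS for safety, so the contradiction stands until one of the two sections is changed.

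A reader might go further and infer that everyone who stops or changes treatment because of harm disappears from the safety results. The document does not support that. Section 2.5.3 expressly covers withdrawal because of adverse reactions and counts people who fail to complete as drop-outs, and 2.9 keeps analyzable drop-outs in the FAS. Such a participant is lost only if also classed as an excluded case or judged not analyzable. Nor does every added drug lead to exclusion: reason (d) covers only medication that may affect the evaluation, and section 2.5.4 allows rescue medication for angina and has additional drugs recorded.

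A reader might also infer that anyone with an event before week 4, the first scheduled visit after randomization in Table 1, who never returns is lost even from the Safe Set. That is one reading. The article does not say whether a safety visit must be a scheduled one. Adverse cardiovascular events are recorded at any time after enrollment (section 2.6.2), so an unscheduled contact might count. What remains is that the Safe Set wording is narrower than 2.5.3 and leaves the matter open.

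**Conclusion.** The point holds as an internal contradiction about the safety population. Section 2.9 assigns safety to the FAS and leaves the Safe Set without a purpose, while 2.5.3 limits exclusion to efficacy.

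The consequence is conditional. If 2.9 is followed, excluded cases would be missing from the safety results, and some of them may be excluded because of an adverse event. The PPS sensitivity analysis would not bring them back. It is not established that people who stop because of harm are lost in general, nor that adverse event rates will be understated.

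The size cannot be determined from the document, which gives no adverse event, exclusion or non-adherence rates. The fall from 10.0% to 6.9%, 3.6% or 0% rests on assumed counts and on every excluded participant having had an event. It shows only that, with 30 per arm, one to three such cases are enough to change the reported safety profile visibly.

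**What to change.** In section 2.9, replace the assignment sentence with wording such as: *Efficacy will be evaluated on the FAS, with the PPS as sensitivity set; safety will be evaluated on the Safe Set.*

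In the same section, align the Safe Set with 2.5.3: all participants who took at least one dose and have at least one safety record, where any reported adverse event counts as a record. Baseline safety data and a completed scheduled visit should not be conditions for entry. Changing only the name of the set, without this alignment, would leave the two sections in disagreement. Section 2.5.3 already states the rule that is needed and requires no change of substance.

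The cost is two sentences of wording, with no new data, visits or participants. Enrollment is reported as complete, so the change should be made and dated before the group code is broken.

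### Section 2.9 evaluates safety on the Full Analysis Set and leaves the Safe Set unused, contradicting the safety population stated in Section 2.5.3

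*Protocol article*

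**What the plan says.** Section 2.9 (Statistical analysis) defines three sets.

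- The FAS is "the set of qualified cases that completed the study and analyzable drop-out cases, excluding excluded cases".
- The PPS is narrower: protocol-compliant participants who completed treatment and follow-up without other influential drugs or treatments.
- The Safe Set holds cases that "have received at least one dose of medication, possess baseline safety data, and have undergone at least one safety visit".

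It then assigns the analyses in one sentence: "Efficacy and safety will be evaluated based on the FAS, with the PPS used for sensitivity analysis". The Safe Set does not appear in that sentence and is named nowhere else in the article.

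Section 2.5.3 (Removal, dropout, and termination criteria) says who the excluded cases are, judged after the study finishes. Reasons a and b begin "Participants don't meet the inclusion criteria or meet the exclusion criteria; b. Participants don't adhere to the medication regimen". Reason c is the absence of any visit record after treatment. Reason d is "Participants used concomitant medications during the trial that may affect the evaluation of the efficacy and safety of SYF". The section bars these cases from the efficacy analysis and then adds that "the safety analysis should include those who have received at least one treatment and have at least one safety record".

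Section 2.6.3 lists among the safety measures "withdrawals, or treatment modifications caused by AEs".

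**The concern.** The two sections name different safety populations. Take a participant who was treated, has safety records, and is later judged non-adherent. Section 2.5.3 keeps that person in the safety analysis and Section 2.9 removes them. Both instructions cannot be followed.

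The set named in 2.9 is also the less suitable one for safety. Whether someone becomes an excluded case is decided after randomisation, and some of the reasons may be connected with harm. A participant who stays in the study but misses doses because of an adverse event could be judged non-adherent under reason b. Reason d refers in terms to drugs that may affect the evaluation of safety. If such people are removed, the safety tables describe a selected group. The PPS offers no check, because it is more selected still.

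The evaluation of safety is a stated aim of the trial. With 30 participants per group (Section 2.7), each person removed is 1/30 = 3.3% of an arm.

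**Working it through.** The document gives no figure to reproduce here. The check is to follow each kind of participant through the definitions in 2.9 and 2.5.3.

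| Participant | FAS (2.9, used for safety) | Safe Set (2.9, unused) | Safety analysis under 2.5.3 |
|---|---|---|---|
| Treated, safety records, later found ineligible (reason a) | Out | In | In |
| Treated, safety records, judged non-adherent (reason b) | Out | In | In |
| Treated, safety records, interfering drug (reason d) | Out | In | In |
| Treated, no post-treatment visit record (reason c) | Out | Generally out: no safety visit | In only if some safety record exists |
| Withdrew because of an adverse event, with safety records, not otherwise excluded | In if analysable | In | In |
| Never dosed | Depends on case | Out | Out |

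The Safe Set entries in the first three rows and the withdrawal row assume that baseline safety data and a safety visit are available.

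1. The first three rows hold the contradiction. The Safe Set agrees with 2.5.3 in each of them and the FAS does not. The set that 2.9 defines and then leaves idle is the one that nearly matches 2.5.3.
2. The withdrawal row limits the consequence. Section 2.5.3 classes anyone who does not complete the observation period as a dropout, whatever the reason, and names adverse reactions among the reasons for voluntary withdrawal. Section 2.9 keeps analysable dropouts in the FAS. Leaving the study because of an adverse event is therefore not by itself a route out of the FAS.
3. The Safe Set and 2.5.3 differ on one requirement. The Safe Set needs baseline safety data and 2.5.3 does not. A treated participant with a later safety record but no baseline would be out of one and in the other.

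**Direction of any bias (assumed inputs only).** Let p be the true proportion with an adverse event in an arm, q the probability that such a participant becomes an excluded case (not a dropout), and r the same probability for a participant without an event. The proportion seen in the FAS is

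p(1 − q) / [p(1 − q) + (1 − p)(1 − r)].

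The document gives none of p, q or r. With p = 0.20 and r = 0.05 assumed:

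- q = 0.05: 0.19 / (0.19 + 0.76) = 20.0%, no bias
- q = 0.25: 0.15 / (0.15 + 0.76) = 16.5%
- q = 0.50: 0.10 / (0.10 + 0.76) = 11.6%
- q = 0.75: 0.05 / (0.05 + 0.76) = 6.2%

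The rate is understated only when q exceeds r. The spread of results shows that the answer depends on the assumption, so none of these figures is an estimate for this trial.

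**The case against.** The best reply is that 2.9 contains a drafting slip. A Safe Set was defined, 2.5.3 states nearly the same population, and the analysts would presumably use it. That may be so, and nothing in the document shows which section would prevail. It does not rescue the sentence, because the article names a set for safety and its own Section 2.5.3 contradicts it. This is not detail left to an analysis plan that is not shown.

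The objection has more force against stronger readings that a reader might infer.

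- *Safety is compared only among those who tolerated the product.* The text does not support this, since people who withdraw because of an adverse event are dropouts and may be in the FAS. What remains is narrower: participants who stay in the study and are later judged non-adherent, ineligible or on interfering drugs.
- *Dose changes caused by adverse events are bound to be undercounted.* Section 2.6.3 counts such changes as a safety measure. However, 2.5.3 sets no adherence threshold and does not say whether a change made because of an adverse event counts as non-adherence. The loss is possible but not stated.
- *A real imbalance between arms would be hidden.* This is not shown. With q = 0.50 and r = 0.05 in both arms, assumed true rates of 10% and 20% become 0.05 / (0.05 + 0.855) = 5.5% and 11.6%. The difference falls from 10 to 6.1 points, but the ratio stays near 2.1. Masking an imbalance in relative terms would need exclusion to differ between arms, and the document says nothing on that.

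**Conclusion.** Section 2.9 is wrong as written. It assigns safety to a set that omits treated participants whom 2.5.3 requires in the safety analysis, and it gives the Safe Set no role. This follows from the definitions alone and needs no assumption.

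The effect on the safety results is conditional. Event rates would be understated if becoming an excluded case is related to adverse events. The document does not establish that relation, and its size cannot be derived without exclusion and event rates. It would also be too strong to say that these participants will be lost, because 2.5.3 says they stay. The established defect is that the plan gives two incompatible instructions and the analysis section carries the unsuitable one.

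**What to change.** Replace the assignment sentence in 2.9 with:

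> Efficacy will be evaluated on the FAS, with the PPS as sensitivity analysis. Safety will be evaluated on the Safe Set; cases excluded from efficacy under 2.5.3 remain in it if they received at least one dose and have at least one safety record.

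The condition at the end is needed. Never-dosed participants do not belong in the Safe Set, and those without a post-treatment visit will generally not qualify.

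Then align the Safe Set definition with 2.5.3 on whether baseline safety data are required, so that one rule applies throughout.

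Make both changes before unblinding, so that the choice of safety population cannot follow the results. Section 2.2.1 reports enrolment complete and 2.4 has the allocation decoded only after the primary analysis, so the change is needed before that point. The cost is one sentence and one aligned definition, with no new data and no additional participants.
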